
### Fidelity testing

The qualitative researcher will check the information entered onto a randomly selected subset of participants’ care plan/clinical records by the pharmacist by reviewing anonymised clinical care records kept by the PHOENIx team and transferred to the qualitative team. The qualitative researchers will then compare these data against a checklist of the components of the intervention: physical health; mental health; addictions; housing; debt; and social activities. This will be used to provide iterative feedback to the intervention team to ensure fidelity and optimise the delivery of the intervention, and in addition, will address intervention fidelity.

### Process evaluation

Semi-structured interviews with a purposive sample of 15–20 participants in the intervention group, 7–10 health professionals and approximately 10 stakeholders including commissioners/senior health board/homelessness services policy makers and representatives from volunteer sectors will be undertaken in order to explore their views on the trial methods and barriers and facilitators to future implementability. We will use Normalisation Process theory [24] to help us conceptualise the effects of the intervention on the interplay between patient capacity and self-management workload which will help us refine our preliminary logic models (which will be developed early in the pilot study) in relation to the intervention. Interviews will be audiotaped with participant consent and transcribed to provide data for qualitative analysis.

### Statistical analyses

#### Quantitative data

Feasibility measures will be analysed using appropriate summary measures including proportions, along with 95% confidence intervals (based on a normal approximation method for one sample proportions) to describe uncertainty. For clinical measures, the study sample size is too small to allow a reliable analysis of the effect of the intervention on outcomes. No hypothesis testing will be performed and the analysis will be limited to estimates of effect size and measures of uncertainty where appropriate. The primary comparison groups will be composed of those randomised to the trial intervention versus those randomised to the control group (usual care). In the first instance, all analyses will be based on the intention to treat principle, i.e. all participants will be analysed in the intervention group to which they were randomised irrespective of adherence to randomised intervention or protocol deviations. Appropriate summary statistics and differences between groups (e.g. mean differences, relative risks, absolute differences) will be presented, with 95% confidence intervals. A log-binomial regression model will be used for binary outcomes and a linear regression model used for continuous outcomes, adjusting for recruiting city and baseline response (where applicable).

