### Sample size and statistical power

The sample size calculation is based around two of the main feasibility objectives: rate of recruitment and retention. The study will aim to recruit and randomise 100 participants in total. If the total number of eligible persons is 200, this will allow measurement of the recruitment rate with a 95% confidence interval width of approximately 14%. If 70% of those recruited are followed up in terms of measuring ED visits, this will allow measurement of the rate with a 95% confidence interval width of approximately 18%.

At the point of submission of this study protocol, a total of 61 participants have been recruited into the study.

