### Primary outcome measures

The randomisation process and recruitment rate will be measured by the numbers invited to participate, and numbers recruited at baseline. In addition, the retention of those remaining in the trial at 3 months and 6 months follow-up will be measured. Adherence to the intervention will be measured by the proportion of participants attending the intervention at planned visits. The proportion of participants with patient-reported outcomes will be measured by the number of participants who complete assessments at planned visits. Finally, the proportion of participants with routinely collected Emergency Department visits and mortality data available at 6 months will be measured and reported.

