**Outcome data**			
Proportion of participants with Emergency Department visits and mortality data available at 6 months	< 60%	60–70%	> 70%
Proportion of patients with questionnaire booklets completed at 6 months	< 50%	50–60%	> 60%

*PEH* persons experiencing homelessness

The data collected in this pilot study will inform the required sample size for the future definitive trial. It is likely that the primary outcome for the definitive RCT to be a composite outcome of mortality and Emergency Department visits.

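### The normal-approximation interval fixed for all feasibility proportions suits the planned values but breaks down at about 95% and above (about 90% with 50 participants); Wilson or exact limits would cost nothing

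*Protocol article*

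**What the plan says.** Under Statistical analyses, Quantitative data, the protocol article says that feasibility measures will be summarised as proportions with "95% confidence intervals (based on a normal approximation method for one sample proportions) to describe uncertainty". No other method is named for small counts or for proportions near 0% or 100%. The same paragraph rules out hypothesis testing.

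The feasibility measures are the primary outcomes. Among those listed under Primary outcome measures is the "proportion of participants with routinely collected Emergency Department visits and mortality data available at 6 months".

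The section Sample size and statistical power gives the only interval figures in the document. "The study will aim to recruit and randomise 100 participants in total". For recruitment the width is put at about 14%, on the assumption of 200 eligible persons. On follow-up, the premise is "If 70% of those recruited are followed up in terms of measuring ED visits", for which the stated width is about 18%.

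Table 2 (Progression criteria) sets the cut-offs for "Proportion of participants with Emergency Department visits and mortality data available at 6 months" at 60% and 70%. Recruitment has cut-offs of 40% and 50%; retention, adherence and questionnaire completion have 50% and 60%. All are set on proportions, and none refers to a confidence limit.

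**The concern.** The usual meaning of a normal-approximation interval for one proportion is the Wald interval: the estimate plus or minus 1.96 estimated standard errors. It is sound for mid-range proportions at these sample sizes. Near 100% the estimated standard error shrinks towards zero, so the interval becomes too short, can run past 100%, and vanishes when every participant is counted as a success.

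The interval method is a stated choice here, not a detail left open. It applies to all the feasibility proportions, whatever values they turn out to have. Availability of routinely collected records need not depend on a participant attending a study visit, so a value well above 70% is conceivable. If that happened, the reported interval on a primary outcome would overstate how precisely the trial had measured it. The outcome matters for planning, because the protocol expects the definitive trial to use a composite of mortality and Emergency Department visits.

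**Working it through.** **Inputs.** Randomised: 100 (Sample size and statistical power). Eligible persons: 200 (same section). Planned Emergency Department follow-up: 70% (same section). Allocation 1:1 (Randomisation), so about 50 in the intervention arm, taken here as the denominator for adherence. Confidence level 95%, z = 1.96. True proportions of 90% and above are assumptions; the protocol gives none.

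**Step 1: the plan's own widths.** Wald full width = 2 × z × √(p(1−p)/n).
- Recruitment, 100/200: 2 × 1.96 × √(0.5 × 0.5/200) = 2 × 1.96 × 0.03536 = 13.9%. Stated: about 14%.
- Follow-up, 70/100: 2 × 1.96 × √(0.7 × 0.3/100) = 2 × 1.96 × 0.04583 = 18.0%. Stated: about 18%.

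Both are correct. The Wilson widths are 13.7% and 17.7%; the exact (Clopper-Pearson) widths are 14.3% and 18.7%.

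**Step 2: coverage.** For each true p, sum the binomial probabilities of all counts x from 0 to n whose interval contains p.

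| n | true p | Wald | Wilson | Exact |
|---|---|---|---|---|
| 200 | 0.50 | 94.4% | 94.4% | 96.0% |
| 100 | 0.70 | 95.0% | 93.7% | 96.3% |
| 100 | 0.90 | 93.2% | 93.6% | 95.6% |
| 100 | 0.95 | 87.7% | 96.6% | 98.3% |
| 100 | 0.97 | 80.2% | 96.9% | 98.9% |
| 100 | 0.98 | 86.6% | 94.9% | 98.5% |
| 100 | 0.99 | 63.3% | 92.1% | 98.2% |
| 50 | 0.60 | 94.1% | 94.1% | 97.1% |
| 50 | 0.90 | 87.9% | 97.0% | 97.0% |
| 50 | 0.95 | 92.0% | 96.2% | 98.8% |
| 50 | 0.98 | 63.5% | 92.2% | 98.2% |

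Coverage moves unevenly because counts are discrete, which is why n = 50 does better at 0.95 than at 0.90. The pattern is still clear: the Wald interval is close to nominal at the planned values and falls short from about 95% with n = 100 and about 90% with n = 50.

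**Step 3: limits at high counts.** Wilson limits are [p + z²/(2n) ± z√(p(1−p)/n + z²/(4n²))] / (1 + z²/n). For 98/100:
- Wald: 0.98 ± 1.96 × √(0.98 × 0.02/100) = 0.98 ± 1.96 × 0.014 = 0.98 ± 0.027, or 95.3% to 100.7%.
- Wilson: centre 0.9992/1.0384 = 0.962, half-width 0.032, or 93.0% to 99.4%.

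| Observed | Wald | Wilson | Exact |
|---|---|---|---|
| 70/100 | 61.0–79.0 | 60.4–78.1 | 60.0–78.8 |
| 95/100 | 90.7–99.3 | 88.8–97.8 | 88.7–98.4 |
| 98/100 | 95.3–100.7 | 93.0–99.4 | 93.0–99.8 |
| 100/100 | 100–100 | 96.3–100 | 96.4–100 |
| 45/50 | 81.7–98.3 | 78.6–95.7 | 78.2–96.7 |
| 48/50 | 90.6–101.4 | 86.5–98.9 | 86.3–99.5 |

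The Wald upper limit exceeds 100% only at 97 to 99 of 100, or 47 to 49 of 50.

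**Step 4: effect on progression.** At 95/100 the lowest of the three lower limits is 88.7%, against a green cut-off of 70% for data availability. At 45/50 it is 78.2%, against a green cut-off of 60% for adherence. The classification is the same by any method.

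**The case against.** The strongest reply is that the protocol does not expect proportions in the range where the method fails. It plans on 70% for Emergency Department follow-up, and every cut-off in Table 2 lies between 40% and 70%. Across that range the Wald interval performs well; at p = 0.70 with n = 100 its coverage (95.0%) is slightly better than Wilson's (93.7%). Even at 90% with n = 100 the two hardly differ. The case in which Wald fails is also the one in which the green result is least in doubt. This stands, and it limits the weight of the point.

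A reader might go further and infer that the interval figures printed in the protocol are too narrow or exceed 100%. They do not. The two widths given are correct and their coverage is close to nominal. A reader might also infer that near-complete record availability is expected. Nothing in the document says so; the 70% planning figure points the other way.

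Two smaller replies carry less weight. The article never uses the term Wald, and its rounded widths alone do not distinguish Wald from Wilson; but Wald is the ordinary reading of the words. A fallback for extreme counts might be held in an analysis plan that is not shown; but the article fixes one method for all feasibility proportions, so naming a better one there is still worthwhile.

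**Conclusion.** The point holds in a conditional form and is minor. The fixed method is adequate at the planned values. If a feasibility proportion proves to be about 95% or higher with 100 participants, or about 90% or higher with 50, the nominal 95% interval can cover as little as 63% to 88% at the values tabulated, can pass 100%, and has zero width at 100%. The consequence is confined to the reported uncertainty: no progression decision changes, because Table 2 works on proportions and the lower limits in that range are well above the green cut-offs.

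This rests on three assumptions: that normal approximation means the Wald interval; that a high proportion actually occurs, most plausibly for routine Emergency Department and mortality data; and that the intervention arm has about 50 participants.

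**What to change.** In Statistical analyses, Quantitative data, replace the words *normal approximation method* with *Wilson score method* (or *exact Clopper-Pearson method*) for one-sample proportions. The cost is one phrase, with no change to data collection, sample size or progression criteria. The stated widths can stay: Wilson gives 13.7% and 17.7%, which still round to 14% and 18%. If the exact method is chosen, the widths become 14.3% and 18.7%, so the second figure would be better given as about 19%. Exact limits are somewhat wider and conservative; Wilson stays closer to nominal on average. Either is suitable, and the choice is best recorded before the 6-month data are analysed.

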### Randomisation

The researcher will undertake informed consent followed by baseline data collection. The researcher will then call a dedicated randomisation telephone line at the Birmingham Clinical Trials Unit. Participants will be randomised at the level of the individual in a 1:1 ratio to either intervention or usual care. The randomisation list will be generated by an independent statistician at Birmingham Clinical Trials Unit (BCTU) and will stratify by recruiting city (Glasgow or Birmingham), using permuted blocks of varying lengths. The participant will be informed of the treatment allocation immediately after baseline assessment.

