### Withdrawal

Participants will be made aware by the researcher that they can freely withdraw (cease to participate) from the trial at any time. Capacity of the participant to continue in the trial will be assessed by the study researcher during follow-up for the duration of the participant’s time in the trial. If a participant is assessed to have permanently lost capacity, then they will be withdrawn from the trial. Data collected until withdrawal will contribute to outcome assessment.

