### Secondary outcome measures

Secondary outcome measures have been divided into clinical measures, addiction-related measures and social outcome measures. These are listed in Table 1.

**Table 1 Tab1:** Secondary outcome measures

Clinical outcome measures	Addiction measures	Social measures
1. Number and cause of Emergency Department visits measured by patient-reported and routinely collected data at 3 and 6 months 2. Number and cause of primary care general practice visits measured by patient-reported and routinely collected data at 3 and 6 months 3. Mortality measured by routinely collected data at 6 months 4. Medication changes (prescribed) and taken (in the case of opioid substitution therapy where supervised) measured through patient-reported and routinely collected data at 3 and 6 months 5. Number and cause of hospitalisation measured by patient-reported and routinely collected data at 3 and 6 months 6. Intervention acceptability measured by qualitative interviews with patients, the intervention delivery team and stakeholders as an ongoing process evaluation 7. Generic health-related quality of life score and health thermometer score measured by EQ-5D-5L at 3 months and 6 months 8. Frailty measured by Fried’s adapted frailty phenotype at 3 months and 6 months 9. Respiratory health measured by Peak Expiratory Flow Rate, MRC Dyspnoea scale and COPD Assessment Test (CAT) at 3 months and 6 months 10. Blood pressure measured by blood pressure monitors at 3 months and 6 months	1. Number of participants experiencing drug overdoses not requiring an Emergency Department visit and the number of overdoses measured by patient-reported data at 3 months and 6 months 2. Number of participants (and number of times) referred to drug and alcohol services, rehab, mental health and GP, and the numbers attending subsequently measured by patient-reported and routinely collected data at 3 and 6 months 3. Numbers and time to commencement on opiate substitute treatment (OST)/benzodiazepine/heroin-assisted treatment and collecting ≥ 80% of daily doses measured by routinely collected data at 3 months and 6 months 4. Number of participants treated with and time to minimum therapeutic OST dose measured by routinely collected data at 3 months and 6 months 5. Dose of OST measured by routinely collected data at 3 months and 6 months 6. Number of missed appointments (with any team, including irregular discharges) and number of participants with missed appointments measured by routinely collected data at 3 months and 6 months 7. Number of persons and days in prison/criminal justice encounters measured by patient-reported data at 3 and 6 months	1. Housing tenure including night shelters, emergency accommodation measured by self-reported data and those provided by the council or third sector, or care home at 3 months and 6 months 2. Level of debt as self-reported by patients at 3 months and 6 months 3. Criminal justice encounters as self-reported by patients at 3 months and 6 months

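### The 6-month estimates of continuous outcomes could make use of the 3-month values; a single-visit linear regression does not (minor, cheap to improve)

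*Protocol article*

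**What the plan says.** The Quantitative data section of the protocol article fixes the model for continuous outcomes as "a linear regression model used for continuous outcomes, adjusting for recruiting city and baseline response". It mentions neither a repeated-measures structure nor imputation. The same section sets the analysis principle: "all participants will be analysed in the intervention group to which they were randomised irrespective of adherence to randomised intervention or protocol deviations".

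Table 1 (Secondary outcome measures) schedules several continuous outcomes at two follow-up visits. One example is "Generic health-related quality of life score and health thermometer score measured by EQ-5D-5L at 3 months and 6 months". Peak flow, the COPD Assessment Test and blood pressure have the same schedule.

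On people who leave, the Withdrawal section says: "Data collected until withdrawal will contribute to outcome assessment".

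On size, "The study will aim to recruit and randomise 100 participants in total", with 1:1 allocation. Table 2 (Progression criteria) sets Green at more than 60% both for retention at 6 months and for booklets completed at 6 months.

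The Quantitative data section also says that the sample is too small for a reliable analysis of effect, and that the clinical outcomes will be estimated with intervals and not tested.

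**The concern.** A regression of the 6-month value on arm, city and baseline has no place for the 3-month value. Someone seen at baseline and 3 months but not at 6 months adds nothing to the 6-month estimate unless the missing value is imputed.

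Two things are at stake.

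- **Precision.** The 3-month value carries information about the missing 6-month value, and the named model leaves it unused.
- **Bias.** If the chance of being lost depends on the 3-month score, and does so differently by arm, the people left at 6 months are not comparable between arms even after baseline adjustment. Arm-specific loss is conceivable here. The trial is open, and the intervention arm has regular team contact and outreach after non-attendance (Location section), with no such trial contact described for usual care.

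The between-arm differences will be reported with 95% intervals, and EQ-5D-5L is the main measure of benefit in the economic work. They should therefore be as sound as the collected data allow.

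**Working it through.** **1. The plan's own figures.** The sample-size section gives interval widths of about 14% and 18%. With width = 2 × 1.96 × √(p(1−p)/n):

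- p = 0.5, n = 200 gives 13.9%.
- p = 0.7, n = 100 gives 18.0%.

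Both reproduce, and this point does not touch them. The 70% refers to Emergency Department data, not to questionnaires.

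**2. How many people enter a 6-month fit.** At the lower edge of Green, 100 × 0.60 = 60 have a 6-month booklet and 40 do not. At 70% the figures are 70 and 30. If 15% also miss the 3-month visit (assumed) and nobody returns after missing it, 85 are seen at 3 months. Then 85 − 70 = 15 to 85 − 60 = 25 people have a 3-month value that the 6-month fit does not use.

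**3. Where bias comes from.** Let γ be the slope of the 6-month value on the 3-month value, given baseline. Let Δ be the amount by which selection shifts the between-arm difference in 3-month scores (given baseline) among those seen at 6 months. If loss depends only on baseline and the 3-month score, the omitted-variable identity gives

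bias = γ × Δ, with γ = (r36 − rB3·rB6)/(1 − rB3²).

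Take assumed correlations rB3 = 0.6, rB6 = 0.55 and r36 = 0.7. Then γ = (0.70 − 0.33)/(1 − 0.36) = 0.37/0.64 = 0.58. If selection acts alike in both arms, Δ is near 0 and so is the bias. A bias of 0.13 SD needs Δ = 0.13/0.58 ≈ 0.22 SD; a bias of 0.19 SD needs Δ = 0.19/0.58 ≈ 0.33 SD.

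**4. Simulation.** Trials of n = 100, 3,000 or 4,000 per scenario. A regression in those with 6-month data was compared with a likelihood-type estimate that also uses the 3-month value. All correlations and dropout rules are assumptions.

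| Loss after 3 months | 6-month regression | Using both visits |
|---|---|---|
| Usual care only, depends on 3-month score; true effect 0; correlations 0.6/0.55/0.7 | −0.13, −0.15 and −0.19 SD in three runs with different dropout rules | 0.00 to +0.01 SD |
| Same dependence in both arms; true effect 0.30 SD; correlations 0.5/0.4/0.5–0.7 | 0.27 to 0.29 SD | 0.29 to 0.30 SD |
| Opposite dependence by arm (extreme); same settings as the row above | −0.01 to 0.17 SD | 0.30 SD |
| Completely at random | no bias | no bias |

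In the extreme case the bias runs from 0.17 − 0.30 = −0.13 to −0.01 − 0.30 = −0.31 SD. The sign is not fixed: reversing the dropout rule reverses it.

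**5. Precision when loss is at random.** With the first set of correlations the variance is about 5 to 8% lower using both visits. An approximate formula agrees: reduction ≈ ρ²(1 − n6/n3), where ρ is the 3-to-6-month correlation given baseline.

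- ρ² = 0.37²/(0.64 × 0.6975) = 0.31.
- With 80 seen at 3 months and 65 at 6, the reduction is 0.31 × (1 − 65/80) ≈ 6%.

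The second set gives a wider range, from 1 − (0.220/0.222)² ≈ 2% to 1 − (0.229/0.243)² ≈ 11%. The 95% interval width falls by only about 1 to 6%. In two of the opposite-dependence runs the two-visit estimate was slightly more variable (SD 0.235 against 0.233, and 0.258 against 0.250), although it was the unbiased one.

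**The case against.** The case for leaving the text alone is substantial.

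- **Imputation is not excluded.** The article does not say that people without a 6-month value are dropped. Linear regression can be combined with multiple imputation that uses the 3-month values, and an analysis plan not shown may specify it. This stands, so the point is conditional on no imputation.
- **No conflict with intention to treat.** A reader might infer that the model contradicts the statement that everyone is analysed. The sentence says in which group people are analysed, whatever their adherence or protocol deviations. It does not promise that everyone with a missing outcome enters every model. A repeated-measures model would not meet that reading either, since people who miss both visits stay out.
- **No conflict with the Withdrawal section.** A reader might also infer a breach of the rule on data collected before withdrawal. A 3-month value contributes through the 3-month estimate, and the section does not say that it must inform the 6-month one.
- **The bias is assumed.** Both arms have the same assessments, the same researchers follow up both, and each researcher visit earns the same voucher. The outreach serves intervention consultations. No loss rates by arm are given, so a claim that the effect is shrunk picks one direction out of several.
- **Little hangs on it.** Every threshold in Table 2 is a feasibility proportion, there is no hypothesis test, and the likely definitive primary outcome is a composite of mortality and Emergency Department visits. Simulated interval widths were 0.87 to 0.95 SD for the regression under random loss, so 0.13 SD is about one seventh of the interval.

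What remains is that the named model, used on its own, leaves collected 3-month data out of the 6-month estimate, while a standard alternative uses them at almost no cost.

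**Conclusion.** A minor point about the choice of method, not an error or an inconsistency in the protocol article. As written, and without imputation, the 6-month estimates for continuous outcomes are available-case estimates from possibly little more than 60 of 100 people.

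Bias of roughly 0.1 to 0.2 SD arises only if loss depends on the 3-month score differently by arm; the extreme opposite-direction case reached about 0.3 SD. With random loss, or the same dependence in both arms, bias is absent or at most about 0.03 SD. The gain is then a variance about 5 to 8% lower under the reference correlations. Correlations, dropout rules and 3-month attendance are all assumed.

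The stronger readings, that the plan breaks its intention-to-treat statement or its withdrawal rule, are not supported. No progression decision is affected.

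**What to change.** For each continuous outcome measured at both visits, replace the single-visit regression with one repeated-measures model:

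- responses: the 3- and 6-month values;
- fixed effects: arm, time, arm-by-time, city, baseline and baseline-by-time;
- unstructured covariance between the two visits;
- everyone with at least one follow-up value included.

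Report the arm difference at each visit with its 95% interval and the number analysed per arm. If the team keeps the regression, it should name the imputation method, or label the estimates as available-case and give the numbers analysed per arm and visit.

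**Cost.** Wording in the protocol or analysis plan and slightly more programming; no new data. The model relies on data being missing at random given baseline and 3-month values. That is a weaker condition than the single-visit regression needs, but it still cannot be checked from the data. It does not recover people who miss both visits.
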